### Setting and randomization

The recruitment is performed at the call-ups for military service in Oulu arranged by the Finnish Defence Forces and City of Oulu every September. Oulu (65°N 25°E) is a growing university town in the northern Finland of approximately 190 000 inhabitants, of which a substantially high proportion are children and adolescents. The unemployment rate of the young people (<25 years) is relatively high in Oulu (19%) compared to other areas in Finland (14%) [36]. Conscription-aged men provide a large, population-based representative sample of young men. All those determined fit for service, who are granted postponement or are exempted from service (n = 1500) will be included in the intervention study. Annually approximately 35% of the conscription aged men in Oulu area are exempted from service, which is the highest proportion in Finland. Adolescents and young men exempted from compulsory military or civil service comprise of a group with a wide range of psychosocial problems and are a target population for supportive interventions [37]. Based on experience for pilot study conducted in 2011, it is estimated that approximately 15% of the men refuse to participate. Thus, approximately 1280 men are expected to participate. These will be randomly allocated into an intervention (n = 640) and control group (n = 640) using computer-generated random numbers. With an estimated 30% dropout rate there will be 447 boys in each group at the end of the intervention.

### The gamified ICT platform for promoting physical activation

The gamified ICT platform forms the basis for different applications. Contrary to previous solutions, subjects do not exercise while playing the game, but their daily activity and exercise is monitored and rewarded in the gamified service. The gamified platform combines several modules: 1) a virtual coach, i.e. avatar for each participant, 2) a game based on participation of peer groups, and achievements supported by rewards from increased physical activity or reduced sedentary behavior 3) possibility for social networking between peers 4) input on physical activity recordings and feedback, 5) communal youth services for supporting coping and an active lifestyle (e.g. through exercise and social counselling), 6) exercise instructions and personal objectives for long-term fitness improvement based on baseline measurements and activity recordings, 7) tailored information content related to health and wellbeing based on a participant's readiness for changing his exercise behaviour. This readiness is evaluated using a modification of Prochaska's Transtheoretical Model of behaviour change [38,39].

The exercise programs provided by professionals will include instructions to physical activity, aerobic and muscle fitness improvement and weight management. Long-term fitness estimation will be provided. The given health information will be evidence-based.

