### Sample size

The primary outcome variable is the change in the time spent in physical activity of different intensities (sedentary, light, moderate and vigorous). The aim is to lower the proportion of inactive men by one third in the intervention group with no change in the control group. At baseline, the estimated number of inactive men is 212 (27.6%, data from the 2009 call-ups). With study power of 80% and significance level of 5%, the calculated sample size is [(27.6 × (100–27.6) + 18.5 × (100–18.5)]/[(27.6-18.5)^2^] × 7.9 = 335 persons/group.

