### Statistical analysis

Descriptive analyses will be performed utilising the results of the questionnaires and measurements. Absolute and percentage changes from baseline will be calculated for continuous variables. The paired samples t test will be used to compare means of the within group change from baseline, and the t test for independent samples will be used to compare means between the treatment and the control group. The analysis of variance for repeated measures will be used to analyse the intra-group-by-time-effect and the group-by-time interaction and to adjust for possible confounding factors over the study period. The changes in activity and weight during the trial and follow-up will also be examined by multiple linear regression analyses with generalized estimation equations (GEE) to account for correlations between repeated measurements. Association between the response and explanatory factors in the aggregated data will first be analysed using cross tabulation and the Pearson product–moment correlations. Multiple linear and logistic regression analysis using all variables associated with activity level and weight in univariate analyses will be performed to evaluate the determinants of change within the exercise group and the pooled groups. Data will be analysed using both intention to treat and per protocol basis.

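### The activation arm is treated partly through peer groups, but the planned between-arm tests assume independent men, so standard errors are too small if the shared intervention makes peers' outcomes correlated

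*Protocol article*

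**What the plan says.** **Allocation.** The protocol article (Setting and randomization) has men "randomly allocated into an intervention (n = 640) and control group (n = 640) using computer-generated random numbers". The unit is the individual man.

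**Delivery.** The section on the gamified ICT platform lists seven modules. One is "a game based on participation of peer groups, and achievements supported by rewards from increased physical activity or reduced sedentary behavior". Another is a "possibility for social networking between peers". The Objectives also name peer networks as a basis of the method. The Intervention section gives the platform to the activation arm only; controls carry on as usual and wear a monitor without feedback.

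**Analysis.** The Statistical analysis section names paired and independent-samples t tests, repeated-measures ANOVA, linear and logistic regression, and GEE. The stated purpose of the GEE is "to account for correlations between repeated measurements", which is correlation within a man over time. The article mentions no peer-group term, group-level robust error, ICC or design effect.

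**Sample size.** The plan states "With study power of 80% and significance level of 5%, the calculated sample size is" 335 per group, by a formula that treats men as independent. It then expects more: "With an estimated 30% dropout rate there will be 447 boys in each group at the end of the intervention".

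**The concern.** This is individual randomisation with grouping in one arm after allocation. Men who play in the same peer group, earn rewards together and exchange messages may encourage or discourage one another. The Background section relies on that mechanism: it argues that social bonding can be a leading motive in multi-player games and may carry over to physical activation. If so, two activation men from one peer group carry less information than two from different groups, while controls remain independent.

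An independent-samples t test, or GEE clustered on the man, ignores this. With positive correlation the error goes one way: the standard error of the difference is too small, the interval too narrow, and a test of zero average effect rejects too often. A larger trial does not cure this, because at a given group size and ICC the understatement is the same proportion at any sample size.

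**Working it through.** **1. The plan's own figure.** Inputs from the Sample size section: 27.6% inactive against 18.5%, multiplier 7.9 (80% power, two-sided 5%).

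[27.6 × 72.4 + 18.5 × 81.5] / 9.1² × 7.9 = 334.5, rounded up to 335 per group.

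The figure reproduces with no allowance for grouping. With unrounded normal quantiles the same formula gives 333.

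**2. Assumptions.** The article gives no peer-group size (m), rule for forming groups, or ICC. I assume m = 5, 10 or 20 analysed men per group and ICC = 0.01, 0.05 or 0.10, with every activation man in one group.

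**3. Formulas.**
- Activation-arm design effect: DE = 1 + (m − 1) × ICC. Control arm: 1.
- With equal arms and equal variances, true SE / naive SE = √[(1 + DE)/2].
- True error of a nominal 5% test = 2 × [1 − Φ(1.96 / ratio)].
- Power at n per arm = Φ(0.091 / √[(0.276 × 0.724 + DE × 0.185 × 0.815)/n] − 1.96), using the correct SE.

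Example, m = 10 and ICC 0.05:
- DE = 1 + 9 × 0.05 = 1.45.
- Ratio = √(2.45/2) = 1.107.
- 1.96/1.107 = 1.77, so the true error is 7.7%.
- Power at 447 is 84.5%.

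**4. Results.**

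| m | ICC | DE | SE understated by | True error of nominal 5% test | n per arm for 80% power | Power at 447 per arm |
|---|---|---|---|---|---|---|
| 5 | 0.01 | 1.04 | 1.0% | 5.2% | 339 | 89.6% |
| 5 | 0.05 | 1.20 | 4.7% | 6.2% | 361 | 87.7% |
| 5 | 0.10 | 1.40 | 8.7% | 7.4% | 390 | 85.1% |
| 10 | 0.01 | 1.09 | 2.2% | 5.5% | 346 | 89.0% |
| 10 | 0.05 | 1.45 | 9.6% | 7.7% | 397 | 84.5% |
| 10 | 0.10 | 1.90 | 17.0% | 10.4% | 461 | 78.8% |
| 20 | 0.01 | 1.19 | 4.4% | 6.1% | 360 | 87.8% |
| 20 | 0.05 | 1.95 | 17.7% | 10.7% | 469 | 78.2% |
| 20 | 0.10 | 2.90 | 28.4% | 16.0% | 604 | 67.4% |

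**5. Break-even for power.** Under independence, 447 per arm gives about 90%. Solving the power formula for 80% at 447 gives DE of about 1.80. That corresponds to ICC = 0.80/9 ≈ 0.09 at m = 10, or 0.80/19 ≈ 0.04 at m = 20.

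**6. Dilution.** If 30% dropout cuts a group of 10 to 7 analysed men, then at ICC 0.05 DE = 1 + 6 × 0.05 = 1.30 and the true error is about 6.8%. Men who never join a group lower it further.

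**The case against.** Three stronger readings are tempting, and the article supports none of them.

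- **That peers' outcomes are certain to be correlated.** Networking is only a possibility, most of the other modules act on the individual (avatar, activity feedback, personal objectives, tailored information), and nothing says that groups are fixed. The Discussion itself warns of low exposure to web-based programmes. The size of any correlation is unknown, and the assumed range starts at a negligible effect.
- **That the test fails even if the service does nothing.** Because men are individually randomised, similarity that existed before men chose the same group does not by itself invalidate the standard error. Only correlation created by the shared intervention does. If the service affects nobody, the ordinary test keeps its 5% level. The inflated error rates above belong to a narrower null: zero average effect, with some groups moved up and others down. When there is a real average effect, the consequence is an interval that is too narrow.
- **That the trial misses its 80% power.** At 335 per group, power would fall to about 73% (m = 10, ICC 0.05) or 66% (m = 20, ICC 0.05). But 335 is the calculated minimum. At the expected 447 completers the figures are 84.5% and 78.2%.

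It can also be said that a condensed article leaves model details to an analysis plan. That carries some weight, but the article does more than stay silent: it names an independent-samples test for the arm comparison and states what the GEE are for. As written, correlation between men is not covered.

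**Conclusion.** The point holds in conditional form. One arm is delivered partly through peer groups, the other is not, and the stated between-arm methods cannot reflect correlation that the shared intervention may create. If such correlation arises, the standard error of the difference is understated by about 1% to 28% over the assumed range. A nominal 5% test of zero average effect then has a true error of about 5.2% to 16%. A middle case (10 per group, ICC 0.05) gives about 7% to 8%, with the lower end allowing for dropout.

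Every one of these sizes rests on assumed group sizes and ICCs, so the article cannot show that the problem is material, only that the plan does not guard against it. The main issue is the standard error; the recruitment margin absorbs much of the power loss. A change to the plan is worth making because the intervention's own rationale expects peers to influence each other, and membership that is not recorded during the trial may be hard to reconstruct.

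**What to change.** - Record peer-group membership for each activation man during the intervention. The article does not say that the platform holds a group identifier, so this has to be arranged. Because groups may overlap or change, set a rule in advance, for example the first or main group joined.
- Where groups form, replace the independence-based arm comparison with one of two analyses: GEE or regression with standard errors robust to peer-group clustering, or a partially nested mixed model with a random peer-group effect in the activation arm only. Treat controls and activation men who join no group as singletons. With peer group as the GEE cluster, the robust variance also covers repeated measurements on the same man.
- Report the observed ICC and group sizes, and restate power at 447 per arm over a stated ICC range.

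No extra participants or visits are needed. The cost is recording membership, some analysis wording, and possibly slightly wider intervals. If the ICC is near zero, the results will hardly change.

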### Intervention

The 6-month intervention will commence at the call-ups (Figure 1). The activation group utilises the abovementioned online gamified activation platform service, whereas the subjects in the control group will continue their normal lives. All subjects will carry a physical activity monitor and the activity data are saved in a database. The control subjects will use blinded monitors which will not provide any feedback for the participants. The questionnaires and measurements will be repeated at the end of the intervention (6 months). The trial protocol and gamified activation service will be pilot tested in 2012 with a smaller sample.

After the intervention the subjects’ entry into military service will be followed up for a period from 18 to 30 months depending on the initiation and length (6–12 months) of service. The course of the service period will be monitored by the Finnish Defence Forces (FDF) which routinely collects data on health and performance of all conscripts attending service. The group assignment will be blinded to the FDF until the end of military service. Examinations measuring aerobic (Cooper - 12 minute running test) [40] and muscle fitness tests [12] are performed when entering service and repeated after its completion. These data will be collected from approximately 70% of the men due to the estimated exemption. This will provide additional information about the impact of the intervention and show the long-term effectiveness of the method aimed at promoting physical activity. It also demonstrates how the activation intervention affects the onset and completion of military service.

### Outcome measures

The questionnaires and physiological measurements have been tested in the annual call-ups in the Oulu area during 2009–2011. Overall, the response rate to the questionnaire has been at or above 62% (2009 N = 770, 73%, 2010: N = 622, 62%, 2011 N = 825, 65%), and 59% or more (59%, 61%, and 72%, respectively) have participated to the measurements.

#### Main and secondary outcome measures

The main outcome measure is self-determined and objectively measured physical activity. Daily physical activity will be followed using a wrist-worn physical activity monitor, Polar Active (Polar Electro Ltd, Finland) [41-46]. This recorder utilizes frequency and regularity of hand movements adjusted for body parameters and a high agreement with energy expenditure has been observed [46]. The device measures physical activity continuously as metabolic equivalents (MET) per 30 s and as time spent at five different zones (very easy, easy, moderate, vigorous, vigorous+), as well as sleep onset and duration. Self-determined physical activity level will be enquired according to questions widely used in health studies [47].

The type of physical activity (sitting/standing, walking, running, cycling and driving) will be tracked using a smartphone with triaxial accelerometers [48-50]. The recognition is based on different features of the acceleration signal and classification is done using *knn* (k nearest neighbours) and QDA (quadratic discriminant analysis) classifiers. The software has a real-time recognition accuracy of 95% when the phone is in the pocket of the subject’s trousers [50].

The secondary outcome is the proportion of overweight and obese boys.

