**Methods/design:**

Conscription-aged men (18 years) attending compulsory annual call-ups for military service in the city of Oulu in Finland (n = 1500) will be randomized to a 6-months intervention (n = 640) or a control group (n = 640) during the fall 2013. A questionnaire on health, health behaviour, diet and wellbeing is administered in the beginning and end of the intervention. In addition, anthropometric measures (height, weight and waist circumference), body composition, grip strength, heart rate variability and aerobic fitness will be measured. The activation group utilizes an online gamified activation method in combination with communal youth services, objective physical activity measurement, social networking, tailored health information and exercise programs according to baseline activity level and the readiness of changes of each individual. Daily physical activity of the participants is monitored in both the activation and control groups. The activation service rewards improvements in physical activity or reductions in sedentary behaviour. The performance and completion of the military service of the participants will also be followed.

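### The protocol gives two different definitions of its primary outcome, ranks self-report equally with the monitor in an open trial, and sizes the trial for a third quantity

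*Protocol article*

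**What the plan says.** Three places in the Protocol article bear on what decides the trial.

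- **Sample size**, first sentence: "The primary outcome variable is the change in the time spent in physical activity of different intensities (sedentary, light, moderate and vigorous"). Four intensities are listed and none is singled out.
- **Sample size**, next sentences: "The aim is to lower the proportion of inactive men by one third in the intervention group with no change in the control group". The baseline follows: "At baseline, the estimated number of inactive men is 212 (27.6%, data from the 2009 call-ups"). The calculation is introduced by "With study power of 80% and significance level of 5%, the calculated sample size is" and ends at 335 per group.
- **Main and secondary outcome measures**: "The main outcome measure is self-determined and objectively measured physical activity". The monitor is described as giving "time spent at five different zones (very easy, easy, moderate, vigorous, vigorous", the last zone being vigorous+. On the questionnaire side, "Self-determined physical activity level will be enquired according to questions widely used in health studies".

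On masking, the Intervention section has the activation group use the online service while controls carry on as usual. Only two things are described as blinded: the feedback on the controls' monitors, and group assignment towards the Finnish Defence Forces. On what the service promotes, the Abstract says "The activation service rewards improvements in physical activity or reductions in sedentary behaviour".

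**The concern.** Naming the primary outcome is the protocol's own task, and an analysis plan can only build on what the protocol names. Here the two definitions differ in content (time by intensity against activity in general), in method (unspecified against monitor plus questionnaire) and in the number of categories (four against five). The quantity used for sizing is a third one. After the data are in, a reader could not tell from this text which result decides the trial, or whether one, some or all must succeed.

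The equal standing of self-report makes this worse. Men who know that they were given a service to make them more active are then asked how active they are. If the monitor showed nothing and the questionnaire showed a gain, nothing in the text would stop that being reported as success on the main outcome. The Discussion adds that compliance with wearing monitors was low in previous studies. If that happens again, the questionnaire could become the more complete of the two measures.

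**Working it through.** **1. The three definitions side by side**

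| Place | Quantity | Type | Method |
|---|---|---|---|
| Sample size, first sentence | Change in time at four intensities | Continuous, four variables | Not stated |
| Main and secondary outcome measures | Physical activity | Not stated; monitor gives five zones, questionnaire an activity level | Monitor and self-report, unranked |
| Sample size, calculation | Proportion of inactive men | Binary, one variable | Not stated |

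**2. Reproducing the stated sample size**

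Inputs (Sample size): 27.6% and 18.5% inactive, multiplier 7.9.

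[27.6 × 72.4 + 18.5 × 81.5] / (27.6 − 18.5)² × 7.9 = (1998.24 + 1507.75) / 82.81 × 7.9 = 334.5, rounded up to 335.

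The multiplier matches two-sided 5% and 80% power: (1.960 + 0.842)² = 7.85. The pooled two-proportion formula gives 336. So 335 is correct, but for the binary endpoint only. No mean change or standard deviation for time at any intensity enters it.

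**3. Where the 27.6% may come from**

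212 / 0.276 = 768. The Outcome measures section reports 770 questionnaire respondents in 2009, and 212 / 770 = 27.5%. This suggests, without proving it, that the baseline rate is a questionnaire figure and not a monitor figure.

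**4. Chance of at least one false positive, if any one test could win**

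The documents give neither the number of tests, nor their correlation, nor a success rule. All three are assumptions here. Two tests stand for one per method, four for the monitor intensities, five for those plus one self-report variable, and eight for four intensities by both methods. Independent tests: 1 − 0.95^k. Correlated tests: simulation of equally correlated two-sided z tests, 400,000 draws.

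| Tests | Corr. 0 | 0.3 | 0.5 | 0.7 | 0.9 |
|---|---|---|---|---|---|
| 2 | 9.8% | 9.5% | 9.0% | 8.4% | 7.0% |
| 4 | 18.5% | 17.4% | 15.5% | 12.9% | 9.3% |
| 5 | 22.6% | 20.8% | 18.2% | 14.9% | 10.2% |
| 8 | 33.7% | 29.9% | 25.0% | 19.1% | 11.9% |

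Time at the intensities shares a fixed day, so some correlations may be negative. Four tests with correlation −1/3 give 16.8%, which lies inside the same range. For correlations of 0 to 0.7 the range is about 8% to 34%.

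**5. Cost of keeping several primaries with a correction**

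This uses the document's binary effect as a yardstick and the 447 per group expected at the end (Setting and randomization), with the pooled formula and Bonferroni.

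| Tests | Level per test | Needed per group for 80% | Power at 447 |
|---|---|---|---|
| 1 | 0.05 | 336 | 89.9% |
| 2 | 0.025 | 406 | 84.0% |
| 4 | 0.0125 | 477 | 76.9% |
| 8 | 0.00625 | 547 | 69.1% |

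One primary is comfortably powered. With four or more the power falls below the stated 80%.

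**The case against.** The best defence is that the article never says each variable is tested at 5%, nor that any single significant result is success. The 5% appears once, to size one binary comparison. The wording of the main outcome could as well mean that both measures must succeed, and then the error rate would not be inflated. A multiplicity rule is commonly left to the analysis plan, which is not shown. All of this stands. A reader might infer that the trial has an actual false-positive rate well above 5%, but the documents do not support that as a fact.

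Four further limits also stand.

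- Eight tests would need the questionnaire to give time at the same four intensities. The article describes only an activity level, plus sitting time under Questionnaires. The 34% end also needs all eight to be independent.
- A reader might conclude that success has no direction. That goes too far: Objectives expects the activation group to be more active and fit, and Sample size aims to lower the proportion inactive. Direction is open only for single intensities, such as light activity.
- The rewards follow recorded activity, not questionnaire answers, so they are not themselves evidence of biased reporting. The argument rests on the open comparison.
- The monitor is not fully neutral either, because only controls have feedback hidden.

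None of this removes the conflict between the two definitions, the mismatch with the sample size, or the equal rank of an unblinded self-report. These are in the text, and a later multiplicity rule would still need a defined primary outcome to work on.

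**Conclusion.** The point holds as an inconsistency in the primary outcome. Two sections define it differently, neither picks one variable, and the 335 per group is right only for the proportion inactive, which neither definition names. Placing self-report level with the monitor in a trial whose participants know their arm is a poor choice, although the size of any reporting bias cannot be worked out from the document.

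The figure of roughly 8% to 34% is conditional. It assumes two to eight tests, each at an unadjusted 5%, correlations between 0 and 0.7, and success on any one. With correlation 0.9 it would be about 7% to 12%. It shows what the open wording could allow, not what the trial plans to do.

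**What to change.** Reconcile the sample-size and outcomes sections before any outcome data are seen:

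- Name one monitor-based primary variable, state the direction that counts as benefit, and test it at 5%.
- The simplest choice is the proportion inactive as classified by the monitor, because it keeps the link to the calculation. First state the monitor definition of inactive and confirm that 27.6% applies to it. If it does not, redo the calculation with a rate that does.
- If a continuous variable is preferred, such as time at a given intensity, give it its own sample-size calculation.
- Map the five monitor zones to the four named intensities, or use one set throughout.
- Make the other intensities and self-reported activity secondary, and say that self-report alone cannot support a claim of effectiveness.

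The cost is the freedom to claim success on several variables and, depending on the choice, a new sample-size justification. Recruitment need not change if the proportion inactive is kept and its baseline is confirmed: the expected 447 per group then gives about 90% power for the stated effect.
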